## Abstract

**Background:**

Running is a popular form of recreational exercise. Beside the positive effects of running on health and fitness, the risk of a running related injury has to be considered. The incidence of injuries in runners is high and varies from 30–79%. However, few intervention studies on prevention of running related injuries have been performed and none of these studies involved novice runners.

**Methods:**

GRONORUN (Groningen Novice Running) is a two armed randomized controlled trial, comparing the effects of two different training programs for novice runners on the incidence of running related injuries. Participants are novice runners, who want to train for a four mile running event. The control group will train according a standard 8 week training program. The intervention group will use a more gradual, 13 week training program which is based on "the ten percent training rule". During the thirteen week follow up participants register information on running and RRI's in an internet based running log. The primary outcome measure is RRI. An injury is defined as a musculoskeletal ailment of the lower extremity or back, causing a restriction of running for at least one week.

**Discussion:**

The GRONORUN trial is the first randomized controlled trial to study a preventive intervention in novice runners. Many different training programs for novice runners are offered, but none are evidence based.

## Background

Worldwide, running is a sport practiced by many individuals to improve cardio-respiratory function, health and well-being [1]. The Royal Dutch Athletics Federation (KNAU) has estimated that around 12.5% of all Dutch people are running on a regular basis, and that the popularity of running events is still growing. The popularity of running positively contributes to increasing levels of physical activity in the population. This is important, because physical inactivity is associated with the development of several chronic diseases, decreased longevity, loss of physical function and weight control [2]. Running is a feasible way for people to become more active. To start with running, just a pair of shoes is needed.

Although running positively contributes to health, there is also the possibility of a running related injury (RRI). The incidence of RRI's injuries in runners at recreational and competitive level is high and varies from 30% to 79% [3-9]. The wide range in incidence is caused by 1) differences in injury definition, 2) time of follow up, 3) differences in population at risk, and 4) differences in methods used to assess RRI, as well as exposure to running. Taking into account the exposure to running, an appropriate way to describe the incidence of RRI's is to calculate the number of RRI's per 1000 hours of running in the population at risk. Injury incidence per exposure varies from 7 to 59 per 1000 hours of running [3-5,10].

Most injuries in runners are overuse injuries of the lower extremity, caused by training errors, that is, running too much, too soon [11]. The exact cause and risk factors of RRI's are still unclear. However, it can be stated that the aetiology of these injuries is multifactorial and diverse. A review by Van Mechelen [12] proposed four factors that have been significantly related to running injuries: a) lack of running experience, b) previous injury, c) running to compete, and d) excessive weekly running distance.

Randomized controlled trials on the effect of interventions for preventing RRI in recreational runners are hard to find. A large amount of the information about the prevention of RRI's is derived from military recruits during basic training [13-20]. A Cochrane review on prevention of injuries in runners showed three categories of preventive strategies: 1) warming-up, cool down and stretching exercises, 2) use of external devices such as shock absorbing insoles, and 3) modification of training schedule [21]. Unfortunately, none of the interventions showed a significant effect in the prevention of RRI's.

Training is required to develop the ability to run. If the stress stimulus of running is optimal, a positive adaptation of structures will take place. An optimal stimulus along with an adequate recovery time will lead to an increase in strength [22]. With the increasing ability to run, the structures ability to handle applied stress also increases.

To minimize the risk of a RRI, an increase of training duration or intensity by no more than 10% is recommended, i.e. the 10% rule [23]. However, so far no studies have examined the effect of such an increase of training load on injury risk in runners.

The GRONORUN trial is designed to examine the effect of a graded training program for novice runners on the incidence of running related injuries. In the current study, we hypothesize that when the human body gets more time for adaptation to running, the incidence of running related injuries will decrease. The objective of the GRONORUN trial is to evaluate the effectiveness of a 13-week graded training program, using the 10% rule, on the incidence of RRI's in a group of novice runners preparing for a four mile run compared to a commonly used 8-week training program. In this article we describe the design of the GRONORUN trial.

## Methods/design

The GROningen NOvice RUNing (GRONORUN) study is a randomized controlled trial (RCT) with a thirteen week follow-up. Participants were randomized into an intervention group (13 weeks training program) or an active control group (8 week training program). Recruitment of participants for the GRONORUN trial took place in May and June 2005 and data collection started in July 2005. The intervention training program started in the second week of July, 13 weeks before the four mile running event, which took place in October 2005.

The study design, procedures and informed consent procedure were approved by the Medical Ethics Committee (Number 2004/285) of the University Medical Center Groningen (UMCG), The Netherlands. All participants provided written informed consent. Guidelines were followed according to the Consort Statement [24].

### Study population

Recruitment was assisted by advertisements in local media to recruit participants who wanted to start a "beginners program" for the Groningen four mile recreational running event. It was not necessary to ultimately participate in the four mile running event itself. Potential participants were sent written information about the study along with a baseline questionnaire and an invitation for an initial interview at the Center for Sports Medicine of the UMCG.

### Inclusion & exclusion criteria

Healthy participants between 18 and 65 years of age, who had no injury of the lower extremity in the three months prior to inclusion and who had not been running on a regular basis in the previous twelve months were eligible for inclusion in the study. Participants were excluded if there were absolute contraindications for vigorous physical activities according to the American College of Sports Medicine [25], or in case of unwillingness to keep a running log.

### Sample size

A power calculation was carried out for the main outcome variable RRI, using a logistic rank survival power analyses. In other studies on novice runners incidence of RRI varies from 29.5 to 58% in a periods of respectively 13 to 28 weeks [3,8]. For the GRONORUN trial we expected an injury incidence of 30%. With a hypothesized 25% reduction of RRI's in the intervention group compared to the control group, a total of 436 runners (2 × 218) were needed for a power of 80% and an alpha of 0.05. The hypothesized reduction was based on clinical relevance, because no other studies on the prevention of RRI in novice runners were found. Assuming an attrition of 15% in the intervention period, a total of 512 (2 × 256) novice runners were needed to detect an effect of the intervention.

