#### Control group: 8 week training program

The novice runners in the control group received a frequently used beginners training program to prepare for a four mile run. The program started 8 weeks before the start of the Groningen four mile run at the level of a run-walk session with a total of 10 minutes of running and 10 minutes of walking (see Table 1).

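### The 30% expected injury incidence matches a 13-week source, but controls have only 8 weeks of scheduled running, and Sample size neither rescales the rate nor justifies a higher weekly hazard

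*Protocol article*

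**What the plan says.** Sample size in the Protocol article gives two planning sources: "In other studies on novice runners incidence of RRI varies from 29.5 to 58% in a periods of respectively 13 to 28 weeks". The next sentence reads "For the GRONORUN trial we expected an injury incidence of 30" per cent. It gives no period for the 30% and does not say how it was obtained from the sources. The effect is a "hypothesized 25% reduction of RRI's in the intervention group compared to the control group", so the 30% is most naturally the control-arm figure. From this the section concludes that "a total of 436 runners (2 × 218) were needed" "for a power of 80% and an alpha of 0.05", by a method described as "using a logistic rank survival power analyses". It then adds: "Assuming an attrition of 15% in the intervention period, a total of 512 (2 × 256) novice runners were needed".

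Of the control arm, the section on its training programme says: "The program started 8 weeks before the start of the Groningen four mile run". The intervention programme starts 13 weeks before the same event. The Training program section makes running frequency equal in both arms. Methods/design gives a thirteen-week follow-up, and the Abstract has runners keep the internet log over that period.

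**The concern.** A cumulative incidence means something only with its period. The 30% sits beside a 13-week figure of 29.5%, while controls have 8 programme weeks at the same number of sessions per week, roughly 8/13 of the scheduled running weeks. The thirteen-week follow-up gives controls more logging time but no more scheduled running. An injury here must be running related and must restrict running for a week, so weeks without running can add few events or none. The Background itself recommends relating injuries to hours of running, but Sample size does not adjust for exposure.

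If the control arm injures at the source's weekly rate, it supplies fewer first injuries than the plan implies. A neutral result could then be taken as evidence that the graded programme does not work, when the comparison had too few injuries to tell.

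**Working it through.** **Inputs.** Sample size gives 29.5% over 13 weeks, 58% over 28 weeks, 30% expected, a 25% relative reduction, 218 per arm, alpha 0.05 (taken as two-sided) and power 80%. The programme sections give 8 and 13 weeks. The documents state no 8-week incidence and no injury count, so both are derived below.

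**The plan's own figure.** 30% against 22.5% gives HR = ln(0.775)/ln(0.70) = 0.715. Implied first injuries at 2 × 218 are 218 × (0.30 + 0.225) = 65 + 49 = 114. Power = Φ(|ln HR| × √events / 2 − 1.96) = Φ(0.336 × 10.70 / 2 − 1.96), about 43%. For 80% the Schoenfeld formula needs 279 injuries, or about 1063 runners. The 436 therefore does not reproduce. The attrition step does: 436/0.85 = 513, against 512. This shortfall is a separate fault, and 43% is the right baseline for the present point.

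**Rescaling to 8 weeks, constant weekly hazard.** p(8) = 1 − (1 − p(T))^(8/T).
- 13-week source: 1 − 0.705^(8/13) = 19.4%
- 30% taken as a 13-week figure: 1 − 0.70^(8/13) = 19.7%
- 28-week source: 1 − 0.42^(8/28) = 22.0%

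**Front-loaded injuries.** If the source hazard in weeks 1–8 is r times that in weeks 9–13, then p(8) = 1 − 0.705^(8r/(8r+5)). This gives 21.9% (r = 1.5), 23.4% (r = 2) and 25.1% (r = 3).

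**Injuries and power at 2 × 218.** A 25% relative reduction is applied over the shared 8 weeks. Injuries = 218 × 1.75p, HR = ln(1 − 0.75p)/ln(1 − p), and power is as above.

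| Control incidence p | HR | Control injuries | Total injuries | Power |
|---|---|---|---|---|
| 30% (plan) | 0.715 | 65 | 114 | about 43% |
| 19.4% | 0.729 | 42 | 74 | 27% |
| 22.0% | 0.726 | 48 | 84 | 31% |
| 25.1% | 0.722 | 55 | 96 | 36% |

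**All 532 randomised (264 intervention, 268 control), no loss.** Injuries = 268p + 264 × 0.75p. At 30% this is 140 injuries and about 51% power. At 19.4% to 25.1% it is 90 to 117 injuries and about 32 to 42% power.

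**Hazard needed to keep 30% in 8 weeks.** The multiple is 13/8 = 1.625 if 30% is the 13-week figure. Against 29.5% it is (ln 0.70 / 8)/(ln 0.705 / 13) = 1.66, and against the 28-week source (ln 0.70 / 8)/(ln 0.42 / 28) = 1.44. Starting from 30% at 13 weeks, a multiple of 1.25 gives 24.0%, 1.5 gives 28.1% and 2 gives 35.5%.

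**The case against.** The strongest reply is that an unchanged weekly hazard contradicts the trial's own premise. The Background blames injuries on doing too much too soon. The control programme starts at the same level as the graded one and prepares for the same event in five fewer weeks, so a higher weekly hazard is plausible, and about 1.6 times the 13-week source's would restore 30%. This stands as a limit on the claim. A reader might infer that the planned number of injuries cannot be reached, and the documents do not support that. They also do not support the 30% as it stands: Sample size states no such multiple, and the control programme is described as one in frequent use, with nothing to say that it is riskier than what the source runners followed.

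Second, a reader might attribute the whole drop from 80% to 27–36% to the programme length. That is wrong, because the plan's own inputs give only about 43% at 2 × 218.

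Third, the Background lists definition, population and assessment method, as well as follow-up time, as reasons why incidences differ. Rescaling for time alone is therefore an extrapolation, and 19 to 25% is a range under assumptions rather than a figure the sources report.

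Fourth, the result depends on the unstated horizon. If 22.5% is kept for the intervention arm over its 13 weeks, total injuries are about 43 + 49 = 92, and at an unchanged weekly hazard the control figure of 19.7% lies below the intervention's 22.5%. If instead 30% applies to 8 weeks and 22.5% to 13, the intervention reaches 1 − 0.775^(8/13) = 14.5% by week 8. The HR is then 0.44 and 218 per arm gives about 97% power. That reading needs only 113 per arm by a two-proportion calculation, so it is not evidently what was planned. Such a spread is itself a reason to state the horizon.

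Finally, the article does not say whether controls run outside their 8 weeks. If they do, their exposure is longer than assumed here.

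**Conclusion.** The point holds as a planning input that is not supported for this design. The expected control incidence corresponds to 13 weeks, the scheduled control running is 8 weeks, and nothing in Sample size connects the two. At the sources' weekly rates the control incidence would be about 19 to 22%, up to about 25% with early injuries. At 2 × 218 that means about 74 to 96 first injuries against an implied 114, and power of about 27 to 36% against about 43%.

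These figures assume that the 30% is the control-arm value, that control risk is confined to the 8 programme weeks, that the 25% reduction applies over those same weeks, that hazard is constant or front-loaded up to threefold, and that the test is two-sided. They do not show that the trial will fall short. A control-programme hazard about 1.6 times the 13-week source's would remove the deficit, but that assumption has to be written down and defended.

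**What to change.** In Sample size, do one of two things. Either give the expected incidence by arm and by period on the 8-week control basis, with the range of about 19 to 25% and the hazard assumption behind it. Or keep 30%, say that it refers to 8 weeks, and justify the weekly hazard of about 1.6 times the 13-week source's that it requires.

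In either case, state when time at risk starts and ends in each arm, and restate the expected number of first injuries and the power for the 532 runners enrolled. Under Statistical analyses, add that a non-significant result will be interpreted through its confidence interval and not as absence of effect.

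No more runners should be enrolled, since randomisation is complete. The cost is a wording change. The stated incidence and power become less favourable and visibly depend on a hazard assumption.

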### Randomization

After baseline measurements and informed consent, participants were assigned to the intervention training program or the control training program. To ensure that both training groups were equal in terms of injury risk, a stratified randomization was performed. Participants were stratified for current sporting activities status, previous injury, and gender. Based on sporting activities, there are three categories of novice runners. The first category consists of novice runners who already are participating in a sport in which axial load (i.e., running, walking or jumping) is integrated. The second category is formed by novice runners who already are participating in sporting activities without axial load, like swimming and cycling. The third category is formed by novice runners who did not participate in any sporting activities at baseline measurements. In a study by Macera [6], a 74% increased risk was found in runners with a positive history of previous injuries. Since it is not clear whether the high rate of re-injury is caused by incomplete healing of a previous injury or a biomechanical problem, a differentiation in time is made. A distinction can be made between no previous injury, sustaining injured in the last 12 months before baseline measurements, and sustaining injured more than 12 months before baseline measurements. Eighteen strata were formed by gender, previous injury (no, 3–12 months and > 12 months) and sporting activities (no, with axial load and without axial load). From each stratum participants were allocated to intervention or control group by drawing a sealed opaque envelope. Each stratum box contained equal numbers of control and intervention envelopes.

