### Statistical analyses

To evaluate the success of the randomization, baseline values will be analyzed for differences between intervention group and control group, using a chi-square for categorical data and a student's t-test for numerical data. To analyze the primary outcome (i.e., RRI), the Kaplan-Meier method will be used. Once a participant has a RRI his or her survival time will be terminated. To evaluate the effect of the intervention, a log rank test will be used to compare the Kaplan-Meier curves of the intervention group to the control group. Analyses will be performed following the "intention to treat" principle. Differences will be considered statistically significant at p < 0.05. All analyses will be done using SPSS version 12 (SPSS, Chicago, Illinois).

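### The sample size does not reproduce: for 30% versus 22.5% injured, 436 runners give about 44% power, not 80%, and about 1,060 would be needed

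*Protocol article*

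**What the plan says.** The Sample size section gives all the ingredients of the calculation and its result.

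- Method: "using a logistic rank survival power analyses", which I read as a log-rank power calculation. It matches the primary analysis in Statistical analyses, where "a log rank test will be used to compare the Kaplan-Meier curves of the intervention group to the control group".
- Incidence: "For the GRONORUN trial we expected an injury incidence of 30" per cent.
- Effect: "With a hypothesized 25% reduction of RRI's in the intervention group compared to the control group", chosen on grounds of clinical relevance.
- Result: "a total of 436 runners (2 × 218) were needed for a power of 80% and an alpha of 0.05".
- Attrition: "Assuming an attrition of 15% in the intervention period, a total of 512 (2 × 256) novice runners were needed".

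On the significance level, Statistical analyses adds only that "Differences will be considered statistically significant at p < 0.05"; whether the test is one- or two-sided is not stated. Allocation is 1:1 (Randomization: "Each stratum box contained equal numbers of control and intervention envelopes"). Participant flow reports 532 randomised, 264 to intervention and 268 to control.

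**The concern.** A fall from 30% to 22.5% is a modest difference in a fairly infrequent event. With 218 per arm it means roughly 65 injuries against 49 (0.30 × 218 and 0.225 × 218). That is too few to separate the arms with 80% power, so the stated sample size looked too small for the stated effect.

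The 25% reduction is the effect the authors call clinically relevant. If power for it is close to one half, a non-significant log-rank test says little about whether the graded programme achieves it. A reader relying on the published 80% would give such a result much more weight than it deserves.

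**Working it through.** **Inputs.** Control risk p0 = 0.30. Intervention risk p1 = 0.30 × (1 − 0.25) = 0.225. Allocation is 1:1, alpha 0.05, power 80%. Two assumptions are mine: the test is two-sided, and 30% is the control-arm risk over follow-up. Both are varied below.

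**Required size (Schoenfeld).**

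- Under proportional hazards, HR = ln(1 − 0.225)/ln(1 − 0.30) = ln(0.775)/ln(0.70) = 0.7146, so ln HR = −0.336.
- Events = 4(1.960 + 0.842)² / (0.336)² ≈ 278 (279 rounded up).
- Mean risk = (0.30 + 0.225)/2 = 0.2625.
- Runners = 278/0.2625 ≈ 1,060 (1,063 from the rounded-up 279).
- With 15% attrition: 1,063/0.85 ≈ 1,251.

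Other formulas agree: Freedman gives 284 events and 1,082 runners; two proportions give 1,080 (1,132 with continuity correction).

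**Power at the numbers in the article.** Power = Φ(0.336 × √events / 2 − 1.96), with events = 0.2625 × N.

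| Runners | Expected injuries | Two-sided power |
|---|---|---|
| 436 (planned, evaluable) | 114.5 | 43.5% |
| 452 (532 × 0.85) | 118.7 | 44.8% |
| 512 (planned, no loss) | 134.4 | 49.5% |
| 532 (randomised, no loss) | 139.7 | 51.0% |

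A simulated log-rank test with exponential injury times, all censored at the end of follow-up, gave 42% power at 218 per arm, 49% at 256 per arm and 80% at 530 per arm.

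**Attempts to recover 436.** Total runners for 80% power, Schoenfeld, events rounded up:

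| Reading | Two-sided | One-sided |
|---|---|---|
| 30% vs 22.5% | 1,063 | 839 |
| 30% is the pooled incidence | 880 | 694 |
| 30% is the intervention arm (40% vs 30%) | 698 | 549 |
| 25% means HR 0.75 | 1,422 | 1,119 |
| 25 percentage points (30% vs 5%) | 52 | 40 |
| Control incidence 58%, 25% reduction | 355 | 280 |
| 30% injury-free, injuries 70% vs 52.5% | 223 | 177 |
| 30% injury-free, raised to 37.5% | 1,130 | 890 |

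For the absolute 25-point reading, the two-sided figure rises to at most 86 with the other formulas. None of these readings gives 436.

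**What 436 would fit.** At 30% control incidence and a two-sided test, it fits a fall to about 18.7%, a reduction of about 38% (HR = ln(0.813)/ln(0.70) ≈ 0.58). Keeping the 25% reduction, it fits a control incidence of about 52–53%. One-sided, the corresponding values are a reduction of about 34% or an incidence of about 46%. With all 532 followed, the effect detectable with 80% power (two-sided) is a fall to about 19.7%, a 34% reduction.

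**Attrition step.** 436/0.85 = 512.9 against the stated 512. This is rounding only, so the discrepancy lies in the 436 itself.

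**The case against.** The arithmetic for 30% versus 22.5% is not in dispute. Four points can be made on the other side.

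1. **Two inputs are assumed.** The article does not say that 30% belongs to the control arm, nor that the test is two-sided, and its hypothesis is directional. This stands as a caveat on size. One-sided power is 56% at 436 and 63% at 532, and the required number falls to 549 under the most favourable combination (one-sided, 30% in the intervention arm). All of these still exceed 436.
2. **The fault may be a misreported input.** An incidence of about 52% lies within the 29.5–58% the article cites from other studies, so the calculation may have used a different incidence. This is possible. However, the upper end of that range comes from a 28-week period, this trial follows runners for 13 weeks, and the article expressly chose 30%. Inputs and result still conflict as printed.
3. **More runners were randomised than planned.** Under intention to treat with censoring, runners lost early still contribute some follow-up, so power for the trial as randomised lies between about 45% and 51%. It is therefore fair to speak of about an even chance of missing the hypothesised effect, not of a likely failure. It remains far from 80%.
4. **The article does not say how a null result will be read.** That is correct. The risk of misreading follows from the published power figure, not from any stated intention.

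**Conclusion.** The sample-size statement is wrong as written and must be corrected. Taking 30% as control-arm risk, a 25% relative reduction, proportional hazards and two-sided alpha 0.05, the required number is about 1,060 runners. The stated 436 is too small by a factor of about 2.4 (1,063/436). Power for the hypothesised effect is about 44% with 436 evaluable runners and about 45–51% with the 532 randomised. A one-sided test would raise this to 56–63%. The size of the gap depends on the two unstated inputs, but its existence does not, since none of the readings tried yields 436. Incidence, effect and sample size cannot all be correct.

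**What to change.** Reconcile the Sample size paragraph.

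- State whether the test is one- or two-sided and which arm the 30% describes.
- If 436 came from other inputs, report those inputs in place of the printed ones.
- If the printed inputs stand, replace the 80% claim: for 30% versus 22.5%, 436 evaluable runners give about 44% power (about 45–51% with the 532 randomised), and the effect detectable with 80% power is a relative reduction of about 34–38%.
- Name the method as a log-rank calculation.

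I would also add, though the arithmetic correction does not depend on it, that the result will be judged from the confidence interval for the effect set against the 25% target. A p-value above 0.05 would then not be reported as absence of a preventive effect.

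The cost is restated figures and wording. Recruitment and randomisation are complete, so no participants are added and the planned analysis does not change; the stated power becomes less favourable.
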